### Safety outcome measures

#### Adverse events

An adverse event (AE) is any untoward medical incident in a patient or a clinical investigation participant administered a pharmaceutical product and which does not necessarily have a causal relationship with the study procedure. An AE can therefore be any unfavourable and unintended sign (including an abnormal laboratory finding), symptom or disease temporally associated with the use of a medicinal (investigational) product, whether or not related to the medicinal (investigational) product. [ICH E6 1.2] AEs are therefore difficult to detect in critically ill patients since the physical state leading to ICU admission itself may already lead to severe complications and further deterioration of physical and mental health.

ICU staff will be instructed to pay attention to allergic reactions like exanthema, flushing, urticaria, stridor, bronchospasm, shock and shortness of breath. These observations will be recorded together with the time of onset, duration, cessation, action that were taken, assessment of intensity and its relation to the study treatment. All adverse events will be reported to investigators and recorded by them on the participating patient’s data sheet during their following visits. Other extraordinary or questionable side effects will also be recorded. The occurrence of thromboembolic events will also be registered until the participating patients are discharged from the hospital.

Serious adverse events (SAEs) are classified as any medical occurrence that results in death, is life-threatening, requires prolongation of existing hospitalisation, or results in persistent or significant disability/incapacity. SAE reporting is required from the responsible Swiss authorities. The third criterion from the SAE definition will be excluded in our trial, as the occurrence of severe bleeding generally leads to prolongation of ICU and/or hospital stay.

A serious unexpected adverse drug reaction (SUSAR) indicates an adverse drug reaction that is of a nature or a severity inconsistent with the applicable product information. Transfusion-related side effects will therefore not be declared as SUSAR.

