^g^Including von Willebrand factor ristocetin cofactor (VWF:Rco); factors II, V, and VII; INR; and platelets count and level of thrombin

^h^Beriplex, Cyklokapron, Konakion, Kyberin, Fibrogammin, NovoSeven, ionised calcium, etc. (see Additional file 1: Table S1)

**Table 3 Tab3:** ICU follow-up data to be assessed within the 48-hour study period beginning at study drug administration

	***Metavision®***	RedCap®
Administration of study medication (or placebo)		
Platelet function analysis (VerifyNow® ADP test) 30–60 min after administration of study drug		X
Check if informed consent is possible		X
Amount of blood loss since drug administration		X
Cause of bleeding (if occurred)		X
SOFA score	X	
Vital parameters^a^	X	
Lowest temperature measured^b^		X
Acidosis occurred (pH < 7.35)		X
Duration of acidosis		X
Full blood count^c^	X	
Coagulation laboratory^d^	X	
ROTEM	X	
Level of vWF and FVIII	X	
Haemoglobin concentration	X	
Fluid balance^e^	X	
Number of given RBCs	X	
Number of given FFPs	X	
Number of given platelet concentrates	X	
Amount of Prothromblex after study intervention	X	
Amount of tranexam acid after study intervention	X	
Amount of fibrinogen after study intervention	X	
Name/amount of other given coagulation products^f^	X	
Number of revision surgery for haemorrhage control		X
Transfusion-related side effects (AE, SAE, see 3.7)^g^		X
Thromboembolic events		X
Any recurrent bleeding such as cerebral haemorrhage, DIC		X

^a^Blood pressure, pulse, SpO_2_, ScvO_2_, SvO_2_ and respiratory rate

^b^Lowest temperature measured since ICU admission

^c^Hemoglobin, leucocytes, erythrocites, haematocrit, mean corpuscular volume (MCV), mean corpuscular haemoglobin (MCH), mean corpuscular haemoglobin concentration (MCHC), red cell distribution width (RDW), thrombocytes, quick, international normalised ratio (INR), activated partial thromboplastin time (APTT), thrombin time 1 (TZ1), and fibrinogen^d^ including factors II, V and VII; INR; platelets count; and level of thrombin

^e^Since ICU admission until 48 h after the study drug administration

^f^Beriplex, Cyklokapron, Konakion, Kyberin, Fibrogammin, NovoSeven, ionised calcium, etc. (see above)

^g^48-h observation period

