## Adherence to intervention protocols

Each time a platelet concentrate is prescribed, a red flag will appear in our data monitoring system. The vWF kit from Basel (HemosIL^2^) will be used to measure the vWF activity (vWF:Ac). The vWF:Ac is measured at four individual times per patient: baseline, 30 min after the thrombocyte concentrate administration has ended, the following day at 6 AM and the day after at 6 AM.

Because the study medication is only a few millilitres and should be given at least 5 min before giving platelets, handling it only for a few minutes will be enough to get it to room temperature, so the study medication will be kept in the fridge until randomisation.

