## Blinding

The patient and the treating medical team will be blinded for the treatment. Wilate® and placebo are both provided with a syringe for drawing up the solution. Furthermore, the carton of Wilate® contains 2 Mix2Vial adapter (one for each vial), which is required for the preparation of Wilate®. Wilate® 1000 IU or placebo (sodium chloride 0.9% Fresenius) will be packed in identical-looking opaque cartons. The preparation occurs by unblinded site personnel.

The randomisation list will be maintained with a study-independent chief consultant and will be kept in a secured place in the ICU. To provide all-time immediate emergency unblinding, the storage location will be communicated to the research team. In case emergency unblinding is needed, a member of the study team will ask a study-independent physician to consult the randomisation list.

After the inclusion of all planned participants, the blinded data will be transferred to the responsible statistician for analysis and processing. A blinded analysis is planned after the recruitment of all 120 patients to assess the pre-defined effect size. In case of SAE, the patient will be unblinded for the trial arm.

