In case the participant is able to give consent, he or she should read and consider the statement before signing and dating the informed consent form and should be given a copy of the signed document. The consent form must also be signed and dated by the investigator (or his designee) at the same time as the participant sign, and it will be retained as part of the study records.

Equally, the next of kin should read and consider the statement before signing and dating the informed consent form and should be given a copy of the signed document. The consent form must also be signed and dated by the investigator (or his designee) and it will be retained as part of the study records.

After recovery, the patient will be informed about his participation in the trial and he/she will have the possibility to withdraw his data from the study. On the consent form, participants will be asked if they agree to the use of their data should they choose to withdraw from the trial, since this trial does involve study-specific collecting blood specimens for the VerifyNow® ADP test and the vWF:Rco test. In case of ex-post-study withdrawal, patient data will be destroyed and therefore not be used for publication upon the patient’s wish.

If the participant dies and could not give consent or no next of kin could be contacted for consent (i.e. consent from an independent physician only), recorded data will still be used as the subgroup of patients dying after haemorrhage is highly relevant for data analysis and interpretation. Moreover, as these are critically ill patients, death unfortunately is not a rare event in the ICU.

The investigator affirms and upholds the principle of the participant’s right to privacy and that they shall comply with applicable privacy laws. Especially, the anonymity of the participants shall be guaranteed when presenting the data at scientific meetings or publishing them in scientific journals. Individual subject medical information obtained as a result of this study is considered confidential and disclosure to third parties is prohibited. Subject confidentiality will be further ensured by utilising subject identification code numbers. As indicated in the informed consent forms, there will be no compensation for trial participation.

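### The unconditional rule to unblind after an SAE, and post-dose vWF levels held in the ICU's own data system with no masking stated, leave two ways for the transfusing team to learn or guess the arm within the 48 h outcome window

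*Protocol article*

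**What the plan says.** All references are to the protocol article.

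- **Blinding, who is blind:** "The patient and the treating medical team will be blinded for the treatment".
- **Blinding, emergency route:** "In case emergency unblinding is needed, a member of the study team will ask a study-independent physician to consult the randomisation list".
- **Blinding, SAE rule:** "In case of SAE, the patient will be unblinded for the trial arm". No cause, relatedness, expectedness, time or recipient is attached.
- **Adverse events:** an SAE is "any medical occurrence that results in death, is life-threatening, requires prolongation of existing hospitalisation, or results in persistent or significant disability/incapacity". The same section then drops the prolonged-hospitalisation criterion for this trial.
- **Serious adverse reactions:** SAEs are looked for on every shift at the bedside. Reporting is due within 7 days if fatal and within 15 days otherwise.
- **Number of transfusions:** the primary outcome counts blood products given in the first 48 h after allocation.
- **Adherence to intervention protocols:** "The vWF:Ac is measured at four individual times per patient", namely at baseline, 30 min after the platelets have run in, and at 6 AM on each of the next two days.
- **Table 3 (48 h follow-up data):** the row "Level of vWF and FVIII" is marked in the Metavision column. The section on electronically documented assessments names Metavision as one of the unit's patient data management systems.
- **Experimental and control intervention:** 2000 IU vWF plus 2000 IU FVIII against saline.

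**The concern.** The primary outcome is a count of decisions. The clinicians who are meant to be blind order the products that are counted, and the article states no fixed threshold for ordering them. Such an outcome relies on blinding more than, say, mortality does, because a clinician who knows or suspects the arm may hold back or give a unit accordingly.

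The plan opens two routes to that knowledge. The first is the SAE rule: the emergency route already covers clinical need, so the extra sentence only adds unblinding where no such need exists. The second is the laboratory. The trial infuses vWF and FVIII, measures them before and after, and assigns the results to the system the ICU runs on. If either route operates within 48 h, part of an observed difference could come from expectation and not from the drug.

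**Working it through.** The plan states no figure on this point, so there is none to reproduce. The total of 120 comes from a simulation on historical data whose mean and dispersion are not given; it is used below only to set a plausible standard error.

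**1. Can the SAE rule act inside the outcome window?**

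| Element | What the article fixes |
|---|---|
| Outcome window | 48 h |
| SAE detection | every shift, at the bedside |
| SAE criteria kept | death, life-threatening, lasting disability |
| Condition on unblinding | none |
| Time and recipient of unblinding | not stated; treating team not excluded |
| Reporting deadline | 7 or 15 days |

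A fatal SAE ends the patient's count, so later disclosure cannot change it. Non-fatal SAEs within 48 h remain. The reporting deadlines fall well after 48 h, so reporting does not require bedside disclosure during the window.

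**2. How visible is the dose in the vWF result?**

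Inputs: 2000 IU vWF (Experimental intervention). Half-life about 12 h, because the article equates 48 h with roughly four half-lives (vWF/VIII concentrate given before study inclusion): 48/4 = 12. Plasma volume 25–40 dL is an assumption. Losses through bleeding are ignored.

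Added level at time t = (2000 / plasma volume) × 0.5^(t/12)

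| Time after dose | 25 dL | 40 dL |
|---|---|---|
| 1 h | 75.5 | 47.2 |
| 6 h | 56.6 | 35.4 |
| 12 h | 40.0 | 25.0 |
| 24 h | 20.0 | 12.5 |
| 48 h | 5.0 | 3.1 |

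(IU/dL.) The first post-dose sample falls 30 min after the platelets end, so 1 h is an approximation. That sample is the revealing one; the two morning samples say progressively less. The baseline sample makes a change easier to read.

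**3. What could unmasking do to the test?**

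This is an illustration only. Take a control mean of 4 units and dispersion k = 1.46 (both assumed), two-sided 5% and 80% power. These values agree with the planned group size:

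n per arm = (1.960 + 0.842)² × [(1/4 + 1/2) + 2 × 1.46] / (ln 0.5)² ≈ 60

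With no true effect, SE = √[(2/4 + 2 × 1.46)/60] = 0.239. Let a share f of active-arm patients be unmasked, and let that knowledge lower their count by a fraction x. The apparent rate ratio is 1 − f·x, and

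type I error = Φ(d − 1.96) + Φ(−d − 1.96), with d = |ln(1 − f·x)| / SE

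| f | x | Apparent ratio | Type I error |
|---|---|---|---|
| 10% | 20% | 0.98 | 5.1% |
| 30% | 20% | 0.94 | 5.8% |
| 50% | 20% | 0.90 | 7.3% |
| 100% | 20% | 0.80 | 15.4% |
| 100% | 30% | 0.70 | 32.1% |

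The first two rows are the scale on which SAE unblinding might work. The lower rows describe a route that reaches most or all patients, as the laboratory results could. The values of f and x are assumed, and unmasked patients are taken to have average use.

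**The case against.** The strongest objection is that the SAE sentence names neither recipient nor time. It follows text on data transfer to the statistician and could mean disclosure for safety assessment after the window has closed. The article condenses a full protocol, where unblinding procedures and system access commonly sit. This stands as a limit: a reader might infer that the treating team is told the arm after every SAE, and the document does not say so. What remains is that the sentence, as written, is unconditional and sits beside a blinding statement and an emergency route with which it is not reconciled. That is a matter of what is stated, not of missing detail.

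Further limits also stand:

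- A reader might infer frequent unblinding concentrated in the heaviest users of blood. The article gives no SAE rate and no relation between SAEs and units. It does say that "death unfortunately is not a rare event in the ICU", but death ends the count, and prolonged stay is not an SAE here. Units given before an SAE could not be affected in any case.
- A reader might infer an early before-and-after pair for FVIII as well. The four sampling times are fixed for vWF activity only. For FVIII the Laboratory parameters section points to routine times, and the baseline coagulation footnote to Table 2 does not list it.
- The Metavision column shows where data are held. Visibility at the bedside, and in time to matter, is inferred from its being the ICU's own system. Against that, Tables 2 and 3 mark the VerifyNow test under REDCap, so separate handling already exists for one study test.
- Baseline vWF varies between patients, so a raised value suggests the arm without proving it.

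**Conclusion.** The point holds as a risk to the blind that the plan's own wording creates. The SAE sentence is unconditional, exceeds the need-based route beside it, does not exclude the treating team, and can act within the 48 h in which that team's orders are counted. The vWF/FVIII results add a second possible route, strongest at the first post-dose vWF sample: about 47–76 IU/dL added at 1 h, given a plasma volume of 25–40 dL, a 12 h half-life and no losses.

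The document does not allow the bias to be sized. On the illustrative assumptions, SAE unblinding of 10–30% of patients moves a 5% test only to 5.1–5.8%. The laboratory route has the larger potential because it could touch every patient, but how far it would depends on visibility and clinician response, neither of which is documented. It would be too strong to conclude that the team will learn the arm or that the trial is in effect open-label. The change is worth making because the outcome is so exposed to clinician knowledge and the remedy is cheap.

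**What to change.** 1. **Blinding section.** Reconcile the SAE sentence with the double-blind statement: replace automatic unblinding after an SAE with the emergency route already described. Where SUSAR reporting needs the allocation, have it released by a person outside the treating and study teams.
2. **Log.** Record every unblinding with its time and who was told, so that unblinding within 48 h can be counted by arm.
3. **Laboratory results.** Report the study-specific post-dose vWF/FVIII results to a restricted field that the treating team cannot see until the 48 h window closes, with access through the emergency route. State this in the Blinding section and correct the Table 3 column to match. If access is already restricted, saying so is enough.

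The cost is a wording change and a result-access setting; sample size and analysis are untouched. The small downside is that the treating team does not routinely see these study-specific values for 48 h. Whether that is acceptable for care is for the investigators to confirm.

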## Patient information and informed consent

The patients do not always have the capacity to give their consent for the study in advance or at all. In this study, the included patients will mostly be emergency cases. For this reason, an independent auditing physician will declare the patient’s suitability for trial participation in the patient’s name as his representative. As such, the independent physician safeguards the participant’s interest and ensures proper medical care. The signed document of the independent physician is the prevailing condition for the inclusion of the patient in our study.

Depending on the general condition of the patient, the investigators will explain to each participant the nature of the study, its purpose, the procedures involved, the expected duration, the potential risks and benefits and any discomfort it may entail upon enrolment. Each participant will be informed that participation in the study is voluntary and that he/she may withdraw from the study at any time and that withdrawal of consent will not affect his/her subsequent medical assistance and treatment.

If anyhow possible, the participant must be informed that his/her medical records may be examined by authorised individuals other than their treating physician.

All study participants will be provided a participant information sheet describing the study and providing sufficient information for the participant to make an informed decision about their participation in the study.

There will also be a consent form for the participant’s next of kin. The patient and next of kin information sheets and the consent forms will be submitted to the CEC to be reviewed and approved. Formal consent of a participant’s next of kin will be sought in non-emergency cases when the participant will be unable to give consent at any time, and if the next of kin is present or reachable over the phone, using the approved consent form. Consent of next of kin in non-emergency cases may be sought even after the inclusion of the patient. In case of ex-post-study withdrawal by the next of kin, patient data will be destroyed and therefore not be used for publication upon the next of kin’s wish.

In case the participant is able to give consent, he or she should read and consider the statement before signing and dating the informed consent form and should be given a copy of the signed document. The consent form must also be signed and dated by the investigator (or his designee) at the same time as the participant sign, and it will be retained as part of the study records.

Equally, the next of kin should read and consider the statement before signing and dating the informed consent form and should be given a copy of the signed document. The consent form must also be signed and dated by the investigator (or his designee) and it will be retained as part of the study records.

After recovery, the patient will be informed about his participation in the trial and he/she will have the possibility to withdraw his data from the study. On the consent form, participants will be asked if they agree to the use of their data should they choose to withdraw from the trial, since this trial does involve study-specific collecting blood specimens for the VerifyNow® ADP test and the vWF:Rco test. In case of ex-post-study withdrawal, patient data will be destroyed and therefore not be used for publication upon the patient’s wish.

If the participant dies and could not give consent or no next of kin could be contacted for consent (i.e. consent from an independent physician only), recorded data will still be used as the subgroup of patients dying after haemorrhage is highly relevant for data analysis and interpretation. Moreover, as these are critically ill patients, death unfortunately is not a rare event in the ICU.

The investigator affirms and upholds the principle of the participant’s right to privacy and that they shall comply with applicable privacy laws. Especially, the anonymity of the participants shall be guaranteed when presenting the data at scientific meetings or publishing them in scientific journals. Individual subject medical information obtained as a result of this study is considered confidential and disclosure to third parties is prohibited. Subject confidentiality will be further ensured by utilising subject identification code numbers. As indicated in the informed consent forms, there will be no compensation for trial participation.

For data verification purposes, authorised representatives of the sponsor, a competent authority (e.g. Swissmedic) or an ethics committee may require direct access to parts of the medical records relevant to the study, including participants’ medical history.

## Safety

During the entire duration of the study, all adverse events (AE) and all serious adverse events (SAEs) are collected, fully investigated and documented in source documents and case report forms (CRF). Study duration encompassed the time from when the participant signs the informed consent until the last protocol-specific procedure has been completed, including a safety follow-up period.

Post-trial management will not differ from management during the study period and patients will be followed as described in the ‘Study period overview’ section.

An individual subject will be excluded from the study in case of the following:Withdrawal of consent by the independent physician or next of kinAn adverse event that in the opinion of the sponsor contraindicates further measuring (emergency setting)

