**Fig. 1 Fig1:**
[figure not shown]
Study flow chart

**Table 1 Tab1:** Study overview

***Visit***	***Screening***	***Treatment***	***Assessment***	***ICU follow-up***		***30-day and 1-year follow-up***^***b***^
*Time (hours, days, weeks)*	*− 1 h*	*0*	*30–60 min*	*1 day*	*2 days*	*12 months*
*Patient information and informed consent*	*x*^*a*^	*x*^*a*^	*x*^*a*^	*x*^*a*^	*x*^*a*^	
*Demographics*	*x*					
*Medical history*	*x*					
*In-/exclusion criteria*	*x*					
*Vital signs*	*x*		*x*	*x*	*x*	
*Platelet function analysis*	*x*		*x*			
*Laboratory tests*	*x*		*x*	*x*	*x*	
*Pregnancy test*	*x*					
*Randomisation*		*x*				
*Information related to bleeding*	*x*		*x*	*x*	*x*	
*Study medication*		*x*				
*Primary outcome variable*			*x*	*x*	*x*	
*Secondary outcome variables*			*x*	*x*	*x*	*x*
*Adverse events*			*x*	*x*	*x*	
*Mortality* *ICU* *Hospital* *30 days* *1 year*				*x*	*x*	*x*

^a^If not possible so far

^b^Assessment of ICU and hospital length of stay, ICU and hospital mortality, 30-day mortality, 1-year mortality, and estimated costs of blood transfusion products

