## Ethical justification

Due to the nature of the condition investigated (severe bleeding representing an emergency setting), patients eligible for study participation will not able to give their consent in most cases. As described above, we will seek the patient’s approval for use of collected data for our publication as soon as feasible.

Severe bleeding is a serious condition calling for immediate intervention. Because ICU length of stay is associated with patient morbidity and mortality we chose to investigate a therapeutic approach that might reduce the need for transfusion products and their possible side effects, thus, leading to shorter ICU and hospital stays and overall better outcomes.

By achieving our goal, we may positively influence patient well-being and enhance satisfaction after severe medical conditions and, most importantly, promote a reduction in patient morbidity and mortality. This in turn would have a positive impact on our society and on the economy.

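### The Safety section starts adverse event collection at the participant's signature, which in this trial often comes after the single dose and conflicts with Table 1, Table 3 and the safety analysis

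*Protocol article*

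**What the plan says.** Two consecutive sentences in the Safety section set the collection period. The first gives its scope: "During the entire duration of the study, all adverse events (AE) and all serious adverse events (SAEs) are collected". The second fixes its limits: "Study duration encompassed the time from when the participant signs the informed consent until the last protocol-specific procedure has been completed", with a safety follow-up period added at the end.

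The consent pathway is described elsewhere.

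- Patient information and informed consent: "In this study, the included patients will mostly be emergency cases". The document that permits entry is not the participant's own: "The signed document of the independent physician is the prevailing condition for the inclusion of the patient in our study". The participant comes later: "After recovery, the patient will be informed about his participation in the trial". The section also foresees participants who never sign ("If the participant dies and could not give consent or no next of kin could be contacted for consent") and keeps their recorded data.
- Ethical justification: "patients eligible for study participation will not able to give their consent in most cases".
- Table 1 marks consent at screening, time 0, 30–60 min, day 1 and day 2, with the footnote "If not possible so far".

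The study drug is given once (Study medication; Study period overview).

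**The concern.** A start date tied to the participant's signature suits a trial in which everyone signs before treatment. Here signature before treatment is expected to be the exception. Under the Safety section's definition, the period for collecting all AEs and SAEs would open after the only exposure for many participants, and would not open at all for those who die unsigned.

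Two things would be at stake if that rule were followed. Reactions close to the infusion, and early thromboembolic events, would lie outside the defined period for those patients. The start would also depend on recovery, which happens after randomisation, so sicker patients would have later and shorter periods. In addition, SAE status triggers reporting deadlines (Serious adverse reactions) and unblinding (Blinding), so it should be clear whether an early event in an unsigned patient falls inside the period.

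**Working it through.** The plan gives no figure to reproduce here. The check is a comparison of the start points in the protocol article, followed by one simple overlap calculation.

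**Start points stated**

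| Place | What is covered | Start |
|---|---|---|
| Safety | All AEs and SAEs | Participant's signature |
| Table 1, adverse events row | Adverse events | First mark at 30–60 min, then day 1 and day 2 |
| Table 3 | Transfusion-related side effects (AE, SAE), thromboembolic events, recurrent bleeding | Study drug, for 48 h |
| Serious adverse reactions | SAEs | Assessed every shift; no start given |
| Adverse events (under Safety outcome measures) | Allergic reactions, with time of onset; thromboembolic events until hospital discharge | No start given |
| Safety analyses | SAEs by severity, transfusion-related side effects, recurrent bleeding, thromboembolic events | Study drug, for 48 h |

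Only the first row depends on a signature.

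**What the Safety rule implies when read literally**

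Let *t* be the hours from dose to the participant's signature. The part of the 48 h analysis period that falls inside the Safety section's collection period is max(0, 48 − *t*) hours for *t* ≥ 0.

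- Signed before or at the dose: all 48 h are covered and there is no conflict.
- Signed at day 1 (*t* = 24): 48 − 24 = 24 h are covered, and the first 24 h are not.
- Signed at day 2 (*t* = 48) or later: 48 − 48 = 0 h are covered.
- Never signed: the period does not open.

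Table 1's consent marks allow any of the first three. The consent section allows signature after recovery and the never-signed case.

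**Can the start points be reconciled as written?**

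They agree only for a participant who signs before the dose. For anyone else the Safety section excludes hours that Table 1, Table 3 and the Safety analyses include. Table 3 does not fully repair this, because its AE/SAE row is limited to transfusion-related effects, whereas the Safety section governs all AEs and SAEs.

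**How many participants are affected?**

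The document says only that emergency cases and inability to consent are the majority situation. It gives no percentage and no distribution of *t*. The number of patients and hours affected therefore cannot be derived.

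**The case against.** The strongest reply is that this is a generic sentence in a protocol whose operational parts are anchored to the dose. Table 3 is explicitly timed from the study drug, Table 1 schedules AEs from 30–60 min, SAEs are reviewed every shift, and the analysis is timed from the drug. The trial has one centre and one study team working from these tables. The signature could also be taken to mean whichever consent document permits inclusion: the physician acts as the patient's representative, and the Safety section itself speaks of consent being withdrawn by the independent physician or next of kin.

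Much of this stands. Collection from the dose is clearly intended, and the Safety section is not the only place that gives a start.

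A reader might therefore go too far in two ways.

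- One inference is that the hours after the dose will go unobserved, or that deaths in unsigned patients will be missed. The document does not support this. The tables cover those hours, mortality is a secondary outcome in its own right, and data from patients who die with only the physician's consent are kept.
- Another is that the comparison between arms will be biased. Nothing in this double-blind design shows that signature timing would differ by arm.

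Two parts of the reply do not stand. Reading the participant's signature as the physician's is strained, because the consent section treats the two as separate acts at separate times. And a dose-anchored table for some safety items does not correct a sentence that sets a different start for all of them.

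**Conclusion.** The point holds as an internal contradiction. The start rule in the Safety section is wrong for a trial in which most participants enter on an independent physician's statement, and it conflicts with Table 1, Table 3 and the Safety analyses section. The conclusion rests on the literal wording and on the protocol's own description of its consent pathway. It needs no assumption about how many patients sign late.

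The document does not establish that safety events will be lost, and it does not allow the effect to be sized. Severity is minor to moderate: worth correcting before safety data are analysed, but no threat to the trial's conclusions as it stands.

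**What to change.** Replace the start point in the Safety section. The sentence could read: AEs and SAEs are collected for every randomised patient from randomisation until the last protocol-specific procedure including safety follow-up, irrespective of whether or when the participant signs consent, and subject to the rules on withdrawal of data. Those rules are in Patient information and informed consent and in Data handling and management, and they need no change.

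Study drug administration would serve equally well as the start and would match Table 3 and the Safety analyses directly. Randomisation has the small advantage of being defined for a patient who is randomised but not dosed, and the 48 h analysis period then lies inside the collection period. Either choice removes the conflict, provided one is named.

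An adverse event mark at time 0 in Table 1 would be tidy but is optional. If the full protocol carries the same sentence, it should be changed there too.

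The cost is one sentence. No visits are added, because Tables 1 and 3 already schedule data for these hours.
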